### Aims of the study

There are two components of BEST; here we present the study protocol of the first phase (BEST-1). The second phase of BEST (BEST-2) will address the question “Is daily azithromycin non-inferior (within 20% margin) to amoxicillin-clavulanic acid in achieving resolution of exacerbations on day 21?” The protocol for BEST-2 will be the subject of a later paper.

This first phase of our proposed national multicentre double-blind double-dummy randomised controlled trial (RCT) is designed to answer our primary questions, as follows. Amongst children with non-CF bronchiectasis, does azithromycin improve the resolution of respiratory exacerbations by day 14 compared with placebo, and does amoxicillin-clavulanic acid improve the resolution of respiratory exacerbations by day 14 compared with placebo?

Our secondary aims are to:

1. determine the effect of azithromycin or amoxicillin-clavulanic acid on the QOL, systemic inflammation, time to next respiratory exacerbation, and duration of exacerbations;

2. explore factors that predict response to antibiotics, including respiratory pathogens (viruses, bacteria, macrolide-resistant bacteria) present in respiratory secretions and blood markers; and

3. describe the point prevalence and diversity of respiratory viruses, *Mycoplasma pneumoniae* and *Chlamydia* species during exacerbations using sensitive molecular detection techniques.

Our study tests the primary hypothesis that both oral azithromycin and amoxicillin-clavulanic acid are superior to placebo in improving the resolution rate of respiratory exacerbations by day 14 in children with non-CF bronchiectasis.

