### Specimen collection

At enrolment (baseline), all children will have a deep nasal swab (NS) specimen collected. In a subset, additional specimens will be collected at baseline and during exacerbations depending on feasibility (some children are unable to attend the study centre at the onset of the exacerbation) and willingness of parents to allow additional venipuncture. These specimens are:

A deep NS specimen for respiratory viruses, respiratory bacterial pathogens (with antibiotic susceptibility testing) and other potentially important respiratory pathogens (*M. pneumoniae, Chlamydia* spp) at baseline and at the beginning and resolution of an exacerbation. The technique used is identical to previous studies [34-36] where the specimens were described as nasopharyngeal swabs. The NSs are handled as per our research laboratory protocol (see below).

Bloods at baseline and at the beginning and end of each exacerbation for C-reactive protein (CRP), neutrophilic marker of inflammation (IL-6) [37], serum amyloid A (SAA) [33,38] and markers of viral infection (interferon gamma-inducible protein 10 (IP-10) and IL-10).

Sputum at baseline and at the beginning and end of each exacerbation (when possible) for lower airway microbiology and antibiotic sensitivity.

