### Sample size

We plan to enrol 189 children (63 per arm), providing 84% power (α = 0.0245, two-sided) to detect a halving of the number of children in the active arm achieving resolution by day 14 (that is, azithromycin or amoxicillin-clavulanic acid: 60% resolved by day 14, compared with placebo: 30% resolved). This is a conservative estimate when compared with our prospective data of persistent symptoms in 24% of children based on the same diary card [50]. As the primary outcome will be obtained in all enrolled children, a drop-out has not been factored in for the intention-to-treat analysis. With 20% drop-out rate, data from 153 children (51 per arm) for ‘per protocol’ analysis provides a study power of 75%. Both treatment arms are compared with the same placebo arm. While the maximum efficiency is attained by allocating more children to the placebo arm (that is, using an allocation ratio of 1:1:√2), we chose to use a 1:1:1 allocation due to ethical concerns of deviating from standard care in respiratory centres.

In the main secondary outcome (PC-QOL), based on a between-group difference of 0.9 (minimum important difference [42]) (SD 0.9), our sample size provides power of 100% (α = 0.05) for data from at least 147 children (that is, assuming at least 80% retention of the 189 children enrolled). For secondary aim 2 (exploring factors that predict response to antibiotics), we will be examining eight main factors and thus a sample size of 147 exceeds the recommended minimum (n = 10 per factor) [51]. The eight factors are smoking, age, underlying aetiology, detection of virus (any versus none, then single versus multiple viruses), presence of azithromycin resistance and blood markers (IL-6, IL-10, IP-10 levels).

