#### For secondary outcomes and aims

For clinical secondary outcomes (secondary aim 1), t-tests or Mann–Whitney will be used for continuous variables (according to normality of data distribution). A Kaplan-Meier curve will be constructed for each group for ‘time to resolution’ and ‘time to next exacerbation’ as done previously [53]. For secondary aim 2 (factors that predict response to antibiotics), univariate analysis will be used to examine the biological factors listed above. Factors that have a *P-*value < 0.2 will be included in a logistic regression model. Potential interactions (for example, virus with bacteria) will be examined in the model. Descriptive data will be used for secondary aim 3 (point prevalence of respiratory pathogens).

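### Secondary aim 2 is sized by counting children rather than outcome events, and its described model names no arm-by-factor term, so as described it would find prognostic factors rather than predictors of antibiotic response

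*Protocol article*

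**What the plan says.** The article lists as its second secondary aim to "explore factors that predict response to antibiotics, including respiratory pathogens" and blood markers (Aims of the study).

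Under Sample size it justifies the number of children for this aim: "we will be examining eight main factors and thus a sample size of 147 exceeds the recommended minimum (n = 10 per factor". The 147 is carried over from the preceding calculation for the cough quality-of-life score, where power is given "for data from at least 147 children (that is, assuming at least 80% retention of the 189 children enrolled". It is therefore a count over all three arms, placebo included. The candidates are then listed: "The eight factors are smoking, age, underlying aetiology, detection of virus (any versus none, then single versus multiple viruses", followed by azithromycin resistance, IL-6, IL-10 and IP-10. Treatment arm is not on the list.

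The section on secondary outcomes and aims gives the method: a univariate screen at P < 0.2, then logistic regression on the factors that pass. On interactions it says: "Potential interactions (for example, virus with bacteria) will be examined in the model". It does not say whether the model uses all children or only those given an antibiotic.

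On the availability of the predictors, the section Specimen collection says: "In a subset, additional specimens will be collected at baseline and during exacerbations depending on feasibility". All children have a nasal swab at enrolment, and the Abstract says that most children give blood and swabs at the later time points.

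**The concern.** There are two separate problems.

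**The unit of the size claim.** How many coefficients a logistic model can support depends on the number of children in the rarer outcome class, not on the number of children. A statement that 147 children exceed ten per factor gives assurance that the event count does not.

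**The estimand.** A factor predicts response to antibiotics if the difference between antibiotic and placebo changes with that factor. That is an arm-by-factor interaction. A main-effects model pooled over arms shows who resolves, whatever was given. A model restricted to treated children also shows who resolves, now without a comparator. The trial has a randomised placebo arm that can separate the two, and the described analysis does not say that it will be used for this.

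At stake is the reading of a result that the Discussion part of the Abstract presents as novel. An association between, say, virus detection and resolution could be read as guidance on which children benefit from antibiotics, when the same association may hold on placebo.

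**Working it through.** **Inputs, all from Sample size**
- Enrolment: "We plan to enrol 189 children (63 per arm), providing 84% power (α = 0.0245, two-sided", three equal arms.
- Planning rates: "azithromycin or amoxicillin-clavulanic acid: 60% resolved by day 14, compared with placebo: 30% resolved".
- Children for this aim: 147, or 147/3 = 49 per arm if retention is equal (my assumption).
- Candidate factors: 8, or 9 coefficients if virus enters as its two stated contrasts.

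**The plan's own figure.** 8 × 10 = 80, and 147 > 80 (147/8 = 18.4 children per factor). The comparison reproduces. 147/189 is 77.8% rather than 80% (0.80 × 189 = 151.2); this has no bearing on the result.

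**Events per factor** = smaller of (resolved, non-resolved) ÷ number of coefficients.

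*All three arms, n = 147*
- Resolved: 98 × 0.60 + 49 × 0.30 = 58.8 + 14.7 = 73.5. Non-resolved: 147 − 73.5 = 73.5.
- Eight factors: 73.5/8 = 9.2. With two virus contrasts: 73.5/9 = 8.2.
- Eight factors plus two arm terms: 73.5/10 = 7.4.
- One pooled active-arm term, eight factors and eight interactions fitted together: 73.5/17 = 4.3.

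*Antibiotic-treated children only, n = 98*
- Non-resolved: 98 × 0.40 = 39.2.
- Eight factors: 39.2/8 = 4.9. With two virus contrasts: 39.2/9 = 4.4.

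Eighty events in the smaller class would need 80/0.50 = 160 children across all arms, or 80/0.40 = 200 treated children.

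**Sensitivity to the rates (assumed ranges).** If resolution in treated children runs from 50% to 76%, the treated-only figure runs from 49/8 = 6.1 down to 23.5/8 = 2.9. In all arms, 70% against 40% gives 58.8/8 = 7.4, and 50% against 30% gives 63.7/8 = 8.0.

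**Specimens.** The three blood markers, and virus and resistance if measured at the exacerbation, depend on specimens taken in a subset. The article gives no fraction. If a fraction f of the 147 is complete and outcome rates are unchanged, the all-arm figure becomes 9.2 × f.

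**The screen.** Selecting at P < 0.2 does not repair the count, because every candidate examined contributes to overfitting, not only those retained.

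**How precise an arm-by-factor estimate would be.** Illustration, with an assumed binary factor at 50% prevalence: 49 active and 24.5 placebo children in each stratum, the full 60% against 30% effect in one stratum and none in the other (30% against 30%).
- Difference in log odds ratios: ln(1.5) − ln(0.4286) = 1.253, a ratio of odds ratios of 3.5.
- Variance = Σ 1/[n p(1−p)] = 1/(49 × 0.24) + 1/(24.5 × 0.21) + 1/(49 × 0.21) + 1/(24.5 × 0.21) = 0.571. Standard error 0.756.
- Power at two-sided 0.05: Φ(1.253/0.756 − 1.96) = Φ(−0.30) ≈ 38%.
- Expected 95% interval: 3.5 divided and multiplied by exp(1.96 × 0.756) = 4.4, or about 0.8 to 15.
- With 70% and 50% in the two active strata against 30% on placebo, power is about 20%.

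**The case against.** Several points on the other side are sound.

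- A reader might infer that the model cannot answer the aim. The article does not support that. The interaction sentence gives virus with bacteria only as an example, so an arm-by-factor term is unnamed, not ruled out. This is an article condensing a fuller protocol, and an analysis plan may exist.
- A reader might infer that counting placebo children is what breaks the ten-per-factor claim. It is not. Without them 98 children remain, and 98 > 80 (12.3 per factor). Placebo children are also needed for any arm-by-factor estimate.
- A reader might take 4.9 per factor as the plan's true figure. It holds only for a treated-only model, which the article does not state.
- The all-arm shortfall, 9.2 against 10, is small for a rule of thumb. Withdrawals and drop-outs count as non-resolved for the primary outcome. If all 189 children were used and had predictors, the smaller class would be 94.5, or 11.8 per factor for eight main effects. The article itself sizes this aim on 147, however.
- The aim is already worded as exploratory, and no power is claimed for it. Screening at P < 0.2 is partly a matter of preference and is not the point here.

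Two things stand after this. The article makes a numerical adequacy claim in the wrong unit for the model it names. It also describes the route to the aim in some detail without the one term that separates response to treatment from prognosis. Both concern what the article states, not detail left out for brevity.

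**Conclusion.** The concern holds in a limited form. Counted in events at the protocol's own rates, the adequacy claim is missed slightly in an all-arm main-effects model (9.2 per factor) and by about half in a treated-only model (4.9). It would also be missed by more than half if all eight interactions were fitted together with a pooled active-arm term (4.3 per parameter). These figures assume 147 children, equal retention across arms and complete predictors; missing specimens lower them by an amount the article does not give. As described, the analysis would identify prognostic factors for resolution. That follows from what is named (eight factors without arm, and one factor-by-factor interaction) and would change if an arm-by-factor term were specified. The point concerns an exploratory secondary aim. It does not affect the primary comparison, its significance level or the stopping rules.

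**What to change.** - State the analysis population: all randomised children with the relevant specimen, at a named time point.
- For each pre-named factor, fit a logistic model of resolution by day 14 with arm, factor and arm-by-factor. Report the interaction with its confidence interval and label it hypothesis-generating.
- Replace the sentence comparing 147 with ten per factor. Suitable content: at n = 147 and the planning rates, about 73 children are expected in the smaller outcome class, fewer where specimens are missing. That is 9.2 per factor for eight main effects only, and about 4.3 per parameter if a pooled active-arm term and all eight interactions are fitted together.

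Fitted one factor at a time with a pooled active-arm term and a single-coefficient factor, the model has three coefficients, 73.5/3 = 24.5 events each. The number of events then no longer threatens the stability of the fit; the limit is the width of the interaction interval, as the illustration shows.

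The cost is wording in a secondary analysis. No further children or measurements are needed. The downside is that the stated adequacy becomes less favourable and the interaction estimates will be imprecise, which the report should say.

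### The sample-size support for the aim-2 logistic model counts children per factor; counted as outcomes, 147 children give 4.9 (antibiotic arms) to 9.2 (all arms) per factor, below 10

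*Protocol article*

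**What the plan says.** In the Sample size section, the protocol article states for secondary aim 2 that "we will be examining eight main factors" and concludes that "a sample size of 147 exceeds the recommended minimum (n = 10 per factor". The factors are smoking, age, aetiology, virus detection, azithromycin resistance, IL-6, IL-10 and IP-10. Virus detection is described with two comparisons: "detection of virus (any versus none, then single versus multiple viruses".

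The model is given under the heading For secondary outcomes and aims. Each factor is first tested alone, and those with a P-"value < 0.2 will be included in a logistic regression model". Interactions are then examined in that model.

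The Sample size section also supplies what is needed to count outcomes: "We plan to enrol 189 children (63 per arm", "we chose to use a 1:1:1 allocation", and the planning rates "azithromycin or amoxicillin-clavulanic acid: 60% resolved by day 14, compared with placebo: 30% resolved". Neither section gives an outcome count for aim 2 or names the arms that enter the model.

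**The concern.** The adequacy statement and the model use different units. Ten subjects per factor is a count of children. In a logistic regression with a yes/no outcome, what the data can support depends on the smaller outcome class. A model in 98 children of whom 39 are non-resolved carries less information than a head count of 98 suggests.

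At stake is how the aim-2 results will be read. The abstract presents the assessment of predictors of antibiotic response as novel, and the Sample size section assures the reader that the model is adequately sized. With few outcomes per candidate factor, fitted odds ratios tend to be too extreme and apparent discrimination too high. A reader who relies on the assurance would not expect this. The primary comparison, the enrolment target and the main secondary outcome are unaffected.

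**Working it through.** **Inputs, all from the Sample size section.** 147 children for aim 2; 189 enrolled (63 per arm); 1:1:1 allocation; 8 factors; 60% resolved by day 14 on each antibiotic and 30% on placebo, so 40% and 70% not resolved. I assume that response in aim 2 means the primary outcome, resolution by day 14.

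**The protocol's own figure.** 147 / 8 = 18.4 children per factor. The minimum of 10 children per factor is 8 × 10 = 80 children, and 147 exceeds it. The statement reproduces when n means children. It also holds for the antibiotic arms alone: 147 × 2/3 = 98, and 98 / 8 = 12.3.

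**The same sizes counted as outcomes.** Outcomes per factor = min(resolved, non-resolved) / 8.

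| Children analysed | Resolved | Non-resolved | Smaller class / 8 |
|---|---|---|---|
| Antibiotic arms of 147 (98) | 98 × 0.60 = 58.8 | 98 × 0.40 = 39.2 | 4.9 |
| All arms of 147 (49 per arm) | 49 × (0.6 + 0.6 + 0.3) = 73.5 | 49 × (0.4 + 0.4 + 0.7) = 73.5 | 9.2 |
| Antibiotic arms of 189 (126) | 126 × 0.60 = 75.6 | 126 × 0.40 = 50.4 | 6.3 |
| All arms of 189 (63 per arm) | 63 × 1.5 = 94.5 | 63 × 1.5 = 94.5 | 11.8 |

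**Dependence on the planning rates.** The smaller class can never exceed half the children. For 147 children the ceiling is 73.5 / 8 = 9.2, which the planned rates happen to reach. For 98 children it is 49 / 8 = 6.1. So at the cited 147, no resolution rate gives 10 outcomes per factor for eight factors.

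**Number of terms.** At 10 outcomes per term, the antibiotic arms of 147 support 39.2 / 10 = 3.9 terms, and all arms of 147 support 73.5 / 10 = 7.4. If the two virus comparisons take two terms, there are nine: 39.2 / 9 = 4.4 and 73.5 / 9 = 8.2. Interactions add more.

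**Pooling the arms.** Placebo children inform response to an antibiotic only through treatment-by-factor terms. As an illustration, one term for antibiotic versus placebo, eight factors and eight products make 1 + 8 + 8 = 17 terms. That gives 73.5 / 17 = 4.3 outcomes per term at 147 children and 94.5 / 17 = 5.6 at 189. The pooled figures of 9.2 and 11.8 are therefore the generous ones.

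**What the shortfall does.** In simulations of eight factors unrelated to the outcome (five binary, three continuous; 98 children, 60% resolved), the full eight-factor model showed a mean apparent AUC of 0.66 where the truth is 0.50. That is the unscreened model, which the protocol does not plan to fit. After the P < 0.2 screen the mean was about 0.61. With 147 children the full model gave about 0.63.

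**The case against.** **The stated minimum is met.** A reader might infer that the protocol breaks its own rule. The documents do not support that. The rule is written as n = 10, and read as children both 147 and 98 satisfy it. The source cited for the rule is not shown, so it cannot be said to mean outcomes. This objection stands against that stronger reading. It does not rescue the assurance, because the rule is met only in a unit that does not measure what a logistic model can bear.

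**The analysis set is inferred.** No section limits aim 2 to the antibiotic arms, and 147 is a three-arm figure. On that basis the count is 9.2 against 10, a small shortfall on a rule of thumb. This stands: 4.9 is conditional on an antibiotic-arm analysis. That analysis fits the aim best, and the pooled alternative needs extra terms.

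**More children may be available.** The protocol counts drop-outs as non-resolved, so all 189 should have a primary outcome. Pooled, they give 11.8, so a reader should not infer that the count falls short on every basis. But the protocol rests its statement on 147, and the antibiotic arms of the 189 still give 6.3. The Specimen collection section restricts some specimens to a subset, which can only lower these numbers.

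**Screening and multiplicity are a separate matter.** A reader might cite the chance that a noise factor passes the screen, or ends with P < 0.05, as proof of too few outcomes. It is not: those chances come from testing eight factors and barely change with sample size. Only the inflated AUC bears on the outcome count, and for the planned screened model it is the smaller figure, about 0.61.

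**Nine terms is not certain.** The two virus comparisons may be successive codings of one factor. The conclusion does not need the ninth term.

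**The aim is exploratory.** The Aims of the study and Sample size sections already describe it in those terms. That limits the consequence but does not justify an assurance of adequacy.

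**Conclusion.** The point holds as a wrong basis for a stated adequacy claim, not as an arithmetic slip. For eight factors in a logistic model, 147 children give 4.9 outcomes per factor if the two antibiotic arms are analysed and 9.2 if all three are pooled. Both are below 10, against 18.4 children per factor as the protocol counts. Ten is reached only with all 189 children pooled (11.8) and no treatment-by-factor terms.

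This rests on 1:1:1 allocation within the 147, on the planned 60% and 30% rates (though no rate lifts the 147-child figures above 6.1 and 9.2), on response meaning resolution by day 14, and on 10 outcomes per factor as a conventional yardstick that the protocol itself does not state. The importance is moderate: it concerns a secondary, exploratory aim, but one whose sizing the protocol affirms.

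**What to change.** In the Sample size section, replace the children-per-factor sentence with the outcome count and name the arms analysed. For example: at the planned rates, about 39 non-resolved children are expected in the antibiotic arms (4.9 per factor), or about 73 in the smaller class over all arms (9.2 per factor). Withdraw the statement that 147 exceeds the minimum for eight factors.

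Under For secondary outcomes and aims, bring the number of candidate terms, including interactions, into line with that count. This could mean fewer factors named in advance, or all eight entered with shrinkage and optimism correction in place of the P < 0.2 screen. The choice between these is one of preference and can be settled in the analysis plan. Carry the exploratory wording already used for the aim through to the reporting of its results.

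The cost is a few sentences and a little analysis code, with no extra patients and no change to the primary analysis. The downside is that the stated adequacy becomes less favourable and, if shrinkage is used, the estimates are pulled towards no effect.

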### Statistical analysis and reporting

Data will be reported and presented in accordance with the updated CONSORT criteria [52]. Children will be analysed according to allocation status (regardless of subsequent management). An interim analysis is planned and a data safety and monitoring committee will determine if the study should be ceased should superiority of any antibiotic be identified after 50% of sample size is achieved.

For our primary aim, the main effects of the interventions will be determined by comparing the primary outcome (resolution of exacerbation) between groups ((azithromycin versus placebo) and (amoxicillin-clavulanic acid versus placebo)). Children who exit the study as clinically worse or drop-outs prior to the end point will be considered non-resolved. Those who exit the study as ‘returned to baseline’ will be considered resolved. Odds ratios will be calculated and, if appropriate, number needed to treat (for benefit) will be expressed. Tests of a treatment arm versus placebo at the end of the study for the primary outcome will be performed at the 2.45% significance level to account for spending some alpha at the interim analysis. Per protocol analysis will be an *a priori* secondary analysis.

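### Fixed 2.45% tests are valid, and 84% is the power of one comparison, but the chance of showing both antibiotics superior is about 75%; Holm's step-down would raise it to about 84% with no extra children

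*Protocol article*

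**What the plan says.** All references are to the Protocol article.

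- **Aims of the study.** Two primary questions are asked, one for each antibiotic against placebo. The section then closes with a joint statement: "Our study tests the primary hypothesis that both oral azithromycin and amoxicillin-clavulanic acid are superior to placebo". The Abstract words the hypothesis the same way.
- **Sample size.** "We plan to enrol 189 children (63 per arm), providing 84% power (α = 0.0245, two-sided"), with planning rates given as "azithromycin or amoxicillin-clavulanic acid: 60% resolved by day 14, compared with placebo: 30% resolved". It adds: "Both treatment arms are compared with the same placebo arm". Allocation is 1:1:1.
- **Statistical analysis and reporting.** "Tests of a treatment arm versus placebo at the end of the study for the primary outcome will be performed at the 2.45% significance level". The only reason attached to this level is alpha spent at the interim analysis.
- **Data safety monitoring committee.** The interim look is at 50% of the sample, at a significance level of 0.001. If only one antibiotic crosses, recruitment goes on in the other antibiotic arm and in placebo.

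**The concern.** Three things do not sit well together.

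1. The hypothesis is worded as a claim about both drugs, but the only power figure attached to the full sample is for one comparison. The article gives no figure for the chance of showing both.
2. Each final test stays at 2.45% whatever happens to the other. Once one antibiotic has been shown superior, only one null hypothesis is left, and keeping it at 2.45% uses about half the error rate that 5% family-wise control allows. If one antibiotic had p ≤ 0.0245 and the other p = 0.03, the second would be reported as unproven, although a valid step-down rule would support the claim.
3. The stated reason for 2.45% does not yield 2.45%. A single look at 0.001 leaves almost all of the 5% for the final test.

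At stake is about 7 to 9 percentage points in the chance of confirming the stated hypothesis, together with a reader's understanding of what the 2.45% protects against.

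**Working it through.** **Inputs.** From Sample size: n = 63 per arm, rates 0.60, 0.60 and 0.30, two-sided α = 0.0245, one shared placebo arm, no drop-out for intention-to-treat. From the monitoring committee section: interim level 0.001 at 50%. The article does not name the test, so several are shown.

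**Step 1. Reproduce the 84%.** One comparison, pooled rate 0.45, critical value z = 2.249.

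- Null standard error: √(2 × 0.45 × 0.55 / 63) = 0.0886.
- Alternative standard error: √((0.60 × 0.40 + 0.30 × 0.70) / 63) = 0.0845.
- With continuity correction 1/63 = 0.0159: Φ[(0.30 − 0.0159 − 2.249 × 0.0886) / 0.0845] = Φ(1.00) = 84.2%.
- Without correction: Φ[(0.30 − 2.249 × 0.0886) / 0.0845] = Φ(1.19) = 88.3%.
- Exact enumeration of Fisher's test: 84.5%.

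So the stated 84% is the power of one comparison with a Fisher or continuity-corrected test.

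**Step 2. Power for both.** Let a(y) be the chance that one antibiotic arm is significant at 2.45% given y resolved in the placebo arm, and b(y) the same at 4.9%. Given y, the two antibiotic arms are independent. Averaging over y ~ Binomial(63, 0.30):

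- both, fixed 2.45%: E[a²]
- at least one: 2E[a] − E[a²]
- both under Holm (smaller p ≤ 0.0245, larger p ≤ 0.049): E[2ab − a²]

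| Test | One comparison | Both, fixed 2.45% | At least one | Both, Holm |
|---|---|---|---|---|
| Fisher | 84.5% | 74.9% | 94.2% | 84.0% |
| Continuity-corrected | 84.5% (exact) | 74.9% | 94.2% | 83.4% |
| Uncorrected chi-square | 88.5% | 80.8% | 96.2% | 88.2% |

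For Fisher, the at-least-one figure is 2 × 84.5 − 74.9 = 94.1, or 94.2 before rounding. A bivariate normal check from 84% per comparison, with correlation 0.21 / (0.21 + 0.24) = 0.467, gives 74.0% fixed and 82.3% with Holm. A simulation of one million trials with the 0.001 look at 32 per arm (Fisher) gives 75.0% and 84.1%.

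**Step 3. What the interim look costs.** By normal theory, a 0.001 look at half the information followed by a final test at 4.9% has a total two-sided error of 4.92%. The interim therefore cannot bring 5% down to 2.45%. The arithmetic (5% − 0.1%)/2 = 2.45% gives the figure exactly.

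**Step 4. Error under Holm.**

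- *Neither drug works.* Holm's first step is the plan's own rule, so the chance of any false claim does not change. By normal theory, interim included, it is about 4.6%; per comparison it is about 2.49%, and twice that is under 5%.
- *One drug works, the other does not.* The ineffective drug can be falsely claimed only at the 0.001 look or at 4.9% in the final test: at most 0.001 + 0.049 = 5% by the union bound. This also covers the case where the first antibiotic crossed at the interim look.
- *Simulated extreme case* (rates 0.30, 0.90, 0.30): Fisher 3.0%, uncorrected chi-square 5.06%. The small excess comes from the chi-square approximation, not from Holm.

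**The case against.** The strongest reply is that the trial is built as two separate comparisons. The Aims pose two questions, the Sample size section powers one antibiotic or the other against placebo, the analysis section lists the two contrasts separately, and the monitoring rules let one antibiotic stop while the other continues. Nowhere is success made conditional on both. This stands. A reader might infer that the 84% is wrong, or that the trial is less powerful than it claims. The documents do not support that: 84% is a correct per-comparison figure, and no joint probability is ever stated that 75% could contradict. Nor is there any inflation of error.

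Two further replies carry weight. If success strictly required both, no split would be needed, and each could be tested at 4.9% (about 84% to 85% joint power). Holm comes within about one point of that and keeps the option of claiming one drug alone, so it serves either reading. Fixed levels also keep each drug's verdict independent of the other's and match simple simultaneous intervals, so the change is not free.

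A reader might also infer that the article attributes 2.45% to the interim alone. It does not use that word, and interim spending fits the small step from 2.5% to 2.45%. The reason given is incomplete rather than contradicted, and correcting it alters no level or sample size.

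It could also be said that multiplicity belongs in an analysis plan. But the article itself fixes the level of each final test and gives a reason for it, so both are open to comment.

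**Conclusion.** The point holds as an efficiency improvement and a labelling correction, not as an error in the power or the type I error. The 84% is right for one comparison and the fixed 2.45% tests are valid. For the hypothesis as worded ("both oral azithromycin and amoxicillin-clavulanic acid are superior to placebo in improving the resolution rate of respiratory exacerbations by day 14"), the chance of success under the planning rates is about 75% with the tests that reproduce the stated power, or about 81% with an uncorrected chi-square. Holm's rule rejects everything the fixed rule rejects and sometimes more, bringing these to about 84% and 88%. The chance of at least one significant result stays at 94% (Fisher).

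These figures assume that both antibiotics achieve 60% and placebo 30%, with 63 children per arm analysed. The gain does not depend on the choice of test; the absolute values do. That 2.45% is a two-way split of 4.9% is an inference from the arithmetic, though a close one. The 75% joint power should not be confused with the 75% in the Sample size section, which is the per-protocol power at 51 per arm.

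**What to change.** Before unblinding, make three changes:

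1. **Testing rule.** Keep the first step at 2.45%. Once either antibiotic has been shown superior, whether at the final analysis or at the 0.001 interim look with the other arm continuing, test the other against placebo at 4.9%. The interim case needs to be written out, because the monitoring rules allow one arm to close early.
2. **Power statement.** Label the 84% as per comparison. Beside it, give the joint power for the test actually planned: about 75% fixed and 84% under Holm for Fisher, or 81% and 88% for an uncorrected chi-square.
3. **Reason for 2.45%.** Say that it reflects two comparisons with placebo as well as the 0.001 interim look, if that is what was intended.

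The cost is a few sentences, with no extra children and no change to the interim rule. The one real downside is that simple simultaneous confidence intervals will not match the Holm decisions exactly; unadjusted intervals can still be reported. If an uncorrected chi-square is used, its slight excess over 5% in extreme cases should be noted; Fisher's test avoids it.
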